### 7.3.2 Location of Face-to-Face Visit Sensitivity Analysis

Participants' face-to-face visits could be conducted in an outpatient clinic or at home. To determine if the location of the visit has an effect on the primary outcome, irrespective of the group allocation, a sensitivity analysis will be performed in which the location of visit is included as a fixed effect covariate, alongside the previously defined adjustments in section 6.2. This fixed effect covariate will have four levels: (i) baseline and 24 month follow-up visit in clinic; (ii) baseline visit in clinic, 24 month follow-up visit at home; (iii) baseline visit at home, 24 month follow-up visit in clinic and (iv) both visits at home. Visits completed not face-to-face (i.e. visits completed remotely due to COVID-19 outbreak) will be excluded from this sensitivity analysis.

### 7.3.3 COVID-19 Sensitivity Analysis

The EMA draft guidance on the implications of COVID-19 on methodological aspects of ongoing trials recommends additional analyses are undertaken to investigate three key phases (pre, during and post COVID-19), in order to understand the impact of the outbreak on the estimated treatment effect. As PD-STAT was nearing completion at the start of the outbreak, only two of these phases (pre and during COVID-19) will be applicable.

The primary outcome, MDS-UPDRS part III scores in the OFF state at 24 months, will be imputed as described in section 4.10.1, despite the fact that there will be more than three items missing for participants assessed during the COVID-19 lock down, due to the limitations of remote data collection outlined in 4.10.3. In order to facilitate a fair comparison between the COVID-19 and non-COVID-19 populations (defined in section 3.3.1), two models will be fitted to all participants' imputed total scores for (i) the COVID-19 population and (ii) the non-COVID-19 population. Interpretation of the analysis will focus on informal comparison of the coefficient estimates of allocated group difference between each model.

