### **Revision 7th August 2020 (Statisticians' blinding maintained)**

At the time of finalising the SAP v1.1 (15/07/2020), it was assumed that all visits undertaken after the introduction of government social distancing measures on 23rd March 2020 would be conducted remotely. As remote visits had not been an option prior to the COVID-19 lockdown, the presence of a remote visit was planned to be used as a proxy/indicator for an outcome measured during COVID-19 lockdown. However, following data export, it became apparent that one participant visit was completed face-to-face shortly after this date, on 25th March 2020. As a result, it was necessary to implement the following revisions to clarify that all outcome collection visits completed after 23rd March 2020 will be considered to be "COVID-19 affected" visits:

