#### 3.1.1 COVID-19 Adaptions

Following the start of the COVID-19 outbreak in early 2020, government guidelines led to a restriction on face-to-face trial visits. As a result, it will be necessary to conduct a small number of primary endpoint (24 month) visits remotely (e.g. using Skype), as well as a number of 26-month visits.

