### **3.3.1 COVID-19 Analysis Populations**

To facilitate sensitivity analyses to explore any effect of the COVID-19 outbreak, two further populations are defined. The non-COVID-19 population will consist of participants whose data collection visits were completed on or prior to the introduction of government social distancing measures on 23rd March 2020. Note different numbers of participants will be included in this population when considering the 24 month and 26 month follow-up visits, due to the timing of the COVID-19 restrictions.

The COVID-19 population will consist of participants who had one or more follow-up visits completed remotely. Again, the numbers of participants included in this population will differ for the 24 month and 26 month end-points.

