Hence  $\alpha$  and  $\beta$  were chosen to reflect the futility design-based hypotheses, with the one-sided  $\alpha$  set at 10% and  $\beta$  at 20% (i.e. 80% power).

Based on a recently reported study at the time of the design of this futility trial, the expected mean increase in MDS-UPDRS part III from baseline to 12 months in the placebo group is assumed to be 2.2 points, with corresponding standard deviation of 7.3 points. Assuming that this increase in MDS-UPDRS part III is linear over time, gives an expected mean increase from baseline to 24 months of 4.4 points in the placebo group (i.e.  $\mu_p = 4.4$ ). Therefore, if we assume the MCID is -3, this implies the mean of the Simvastatin group,  $\mu_s$ , is 1.4 points. Additionally, we assume a slightly inflated standard deviation over this period of 7.5 points.

The sample size calculation was based on a two-sample t-test with a 10% one-sided alpha. Following the previously listed assumptions, the number of participants needed to follow-up at 24 months (i.e. with primary outcome data) is 57 participants per group, to provide 80% power to reject the null hypothesis of non-futility and declare futility.

This sample size was inflated to allow for a proportion of participants allocated to the Simvastatin group to stop taking the trial medication during the initial 1-month low dose phase. Assuming that this proportion was 15%, the above sample size was inflated by  $(1-0.15)^{-2}$ , to give 79 participants per group. Secondly, the sample size was adjusted to allow for a (non-differential) loss to follow-up rate of 20%. Accordingly, the sample size was further inflated by a factor of  $(1-0.2)^{-1}$ , to give a sample size of 99 participants per group and a total recruitment target of 198 participants commencing the higher dose phase of the study.

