#### 4.10.3 Missing Data as a Consequence of COVID-19

Although the majority of outcomes can be completed remotely, due to the nature of some of the tasks, a small number of items/measurements cannot be assessed during remote visits. For the MDS-UPDRS part III, question 3 (rigidity, consisting of 5 items) and question 12 (postural stability, consisting of 1 item) cannot be assessed remotely. This will affect calculation of the primary outcome, total MDS-UPDRS part III assessed in the OFF state, and corresponding secondary outcome assessed in the ON state.

In addition, the ACE-III cannot be completed remotely, whilst completion of 10MWT is dependent on the suitability of the participant's house or outside space and completion of the BTT is dependent on a stable internet connection and the availability of a tablet or computer. Finally, outcomes derived from the blood test at 24 months will be missing for participants in the COVID-19 population.

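### The COVID-19 sensitivity analysis in SAP 7.3.3 sets a very imprecise remote-only model beside a near-repeat of the primary analysis, and 3.3.1 defines its two populations on different bases

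*SAP*

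**What the plan says.** SAP 3.1.1 expects that "it will be necessary to conduct a small number of primary endpoint (24 month) visits remotely". It gives no count.

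SAP 4.10.3 states that "question 3 (rigidity, consisting of 5 items) and question 12 (postural stability, consisting of 1 item) cannot be assessed remotely". SAP 4.10.1 prorates the part III total when no more than three items are missing, and lifts that limit for the sensitivity analyses in 7.3. It also records that most participants already lack the second postural tremor score.

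SAP 7.3.3 applies the relaxed proration and fits two models, to "total scores for (i) the COVID-19 population and (ii) the non-COVID-19 population". Interpretation rests on an informal comparison of the two treatment coefficients.

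SAP 3.3.1 bases the non-COVID-19 population on visits completed by 23 March 2020. The other population is defined by mode: "The COVID-19 population will consist of participants who had one or more follow-up visits completed remotely". The revision entry of 7 August 2020 was prompted because "one participant visit was completed face-to-face shortly after this date", on 25 March. It declares every outcome visit after 23 March to be COVID-19 affected.

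**The concern.** A sensitivity analysis for the pandemic should show whether the futility conclusion depends on how pandemic-affected endpoints were handled. In the primary analysis these endpoints are left out through the item limit. The direct check is to put them back and see whether the estimate, its 80% interval and the test against −3 change.

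Section 7.3.3 does not do this. One of its two coefficients largely repeats the primary estimate. The other comes from remote participants alone and is likely to be dominated by sampling error, so agreement and disagreement between them would both be hard to read. The two populations are also not complements of each other, so a post-lockdown face-to-face endpoint would appear in neither model.

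**Working it through.** **The plan's own figure.** SAP 4.2 uses a "two-sample t-test with a 10% one-sided alpha" and 57 per group "to provide 80% power to reject the null hypothesis of non-futility and declare futility", with a margin of 3 points ("if we assume the MCID is -3") and SD 7.5.

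- n per group = 2 × [7.5 × (1.2816 + 0.8416) / 3]² = 56.4, so 57. Noncentral-t power at 57 per group is 80.1%.
- 57 / 0.85² = 78.9, so 79. Then 79 / 0.8 = 98.75, so 99 per group and 198 in total.

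The stated sample size reproduces, so SD 7.5 and the 3-point margin are used below.

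**Which scores reach the primary analysis.** A remote visit lacks 5 + 1 = 6 items, or 7 where only one tremor score exists. Both exceed three. Section 7.3.3 itself acknowledges that lockdown assessments exceed the limit. The non-COVID-19 model can therefore differ from the primary analysis in only two ways:

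- it may gain earlier participants admitted by the relaxed limit;
- it would lose the 25 March participant, if that was a 24-month visit.

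**Precision of the remote-only model.** Let n be the number of remote 24-month participants, split 1:1. The values of n are assumptions, since the SAP gives none.

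- Unadjusted SE = 7.5 × √(4/n); 80% half-width = t(0.90, n−2) × SE.
- n=6: 1.533 × 6.12 = 9.4. n=10: 1.397 × 4.74 = 6.6. n=20: 1.330 × 3.35 = 4.5.
- Full adjustment under 6.2 uses five covariates (baseline score, gender, age, Hoehn and Yahr, disease duration). The rule in 7.2.1 gives n − 2 − 5 = n − 7 degrees of freedom.

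The adjusted half-widths below are t quantiles times the median SE over 3,000 simulated least-squares designs without a site effect. The power column is for a true 3-point difference between the two coefficients (two-sided 5%). It uses the unadjusted SEs and an assumed reference set of 198 × 0.8 ≈ 158, with SE 7.5 × √(4/158) = 1.19.

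| n (assumed) | Unadjusted half-width | Baseline-only half-width | Full model df | Full model half-width | Power |
|---|---|---|---|---|---|
| 6 | 9.4 | 10.6 | none | not estimable | 8% |
| 10 | 6.6 | 6.9 | 3 | 11.8 | 9% |
| 20 | 4.5 | 4.5 | 13 | 5.2 | 13% |
| 40 | 3.1 | 3.1 | 33 | 3.3 | 20% |

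The difference between coefficients detectable with 80% power is 2.80 × √(SE² + 1.19²): 17.5 points at n=6, 13.7 at n=10, 10.0 at n=20 and 7.4 at n=40.

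**What pooling would show.** If the treatment effect among n remote participants differed by 3 points, including them among 158 would move the estimate by about 3 × n/158: 0.11 at n=6, 0.19 at n=10 and 0.38 at n=20, against an SE of about 1.19. This comparison can be made whatever n turns out to be.

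**Whether another section fills the gap.**

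- 7.3.1 (CACE) could include remote scores under the relaxed limit, but runs only if non-compliance reaches 20%, and it estimates a different quantity.
- 7.3.2 excludes remote visits.
- 7.4.1 lies outside the relaxation for 7.3. It keeps remote participants' baseline and 12-month scores but not their 24-month scores.
- 7.4.2.1 pools all scores with a lockdown indicator, but only among compliers and only if the disease-modifying analysis goes ahead.
- 8.2.1 makes the all-versus-excluding comparison, for secondary outcomes only.

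**The two definitions side by side.** A face-to-face visit on 25 March 2020 is after the date cut-off, so it is not non-COVID-19. It is not remote, so it does not meet the other definition. The 7 August revision nevertheless counts it as COVID-19 affected.

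**The case against.** Several points on the other side have force.

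- **The model is not named in 7.3.3.** Full adjustment follows from 6.2, 7.2 and Table 8. Table 8 also has a baseline-only column, 6.2 promises such fits, and clarification (iii) drops the centre effect from them. That fit can be estimated at n=6. A reader might infer that the remote-only analysis cannot be fitted at all; the SAP does not support that. The baseline-only fit is possible but still imprecise.
- **The comparison is informal.** It has no test and no decision rule, so the 3-point margin is a yardstick and not a criterion the plan set for it. This stands, but an informal comparison still has to be readable, and coefficients this uncertain are not.
- **The stakes are modest.** A few remote scores would move the pooled estimate by roughly 0.1 to 0.4 points on the assumptions above. A reader might infer that the futility conclusion is in doubt; nothing in the SAP supports that, and the primary test itself is unaffected.
- **The 25 March visit is one participant.** The SAP does not say whether it was a 24- or a 26-month visit, and it bears on 7.3.3 only if it was the former. A mode-based population also has a rationale, because items are lost through remote assessment. The mismatch between the two definitions remains.
- **There is partial cover elsewhere.** A triggered CACE analysis could bring in the remote scores. It is conditional, so it does not replace a planned check.

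**Conclusion.** The point holds as one of limited information and inconsistent definitions. Over any plausible small number of remote visits, the comparison in 7.3.3 is uninformative: the half-width of the remote-only interval exceeds 3 points at every assumed n from 6 to 40, and the full model has no residual degrees of freedom at n=7 or below. It would go too far to say that the analysis could never show an impact, because the number of remote visits is not stated and a very large difference might still be visible.

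The substantive gap is that no unconditional analysis shows the futility result with the remote 24-month scores included, while the secondary outcomes do get an all-versus-excluding comparison. The effect on the estimate is probably small, but the plan as written would not demonstrate that. Section 3.3.1 also needs reconciling with the 7 August 2020 revision.

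The conclusion rests on SD 7.5, a 1:1 split among remote participants, a reference set of about 158 and assumed remote counts.

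**What to change.** 1. Add to 7.3.3 one fit of Equation 2 to all mITT participants with the item limit relaxed. Report its coefficient, 80% confidence interval and test against −3 beside the primary result. This carries the 8.2.1 approach over to the primary outcome.
2. Keep any remote-only or group-by-COVID estimate as descriptive only. An additive lockdown indicator alone would not serve, because it measures a shift in score and not a change in treatment effect.
3. In 3.3.1, define the COVID-19 population by a visit dated after 23 March 2020, separately for the 24- and 26-month endpoints.
4. As an optional further check, score every participant at baseline and 24 months on the remotely assessable items only, prorated to 33 items. This keeps the −3 margin on its scale and avoids mixing proration factors of 33/26 = 1.27 (remote, seven items missing) and 33/32 = 1.03 (usual face-to-face). Shortening the score for remote participants alone would mix scales.

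The cost is SAP wording and one extra model. Because SAP version 2.1 records that allocations were revealed by 24 August 2020, the addition should be labelled as made after that point.

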## 7.4 SECONDARY ANALYSES OF THE PRIMARY OUTCOME

### 7.4.1 Repeated Measure Model

To ensure maximal use of the available primary outcome data, a repeated measures, mixed effects model will be fitted to the primary outcome measure at baseline, 12, and 24 months, where participants are included as a random effect.

The model will be adjusted for participant's age at baseline, gender and disease duration, as well as the stratification variables (Hoehn & Yahr score as a fixed effect and recruiting site as a random effect). The model will include visit (baseline, 12 months and 24 months) and the interaction between visit and allocated group, which will be the coefficient of interest.

The repeated measure model is defined as

$$y_{i,j,t} = \delta_1 t + \delta_2 x_{1,i,j} I_{t=12} + \delta_3 x_{1,i,j} I_{t=24} + \theta x_{i,j} + Z_i + U_{i,j} + \varepsilon_{i,j,t}.$$

*Equation 4*

where

- $I_{t=k} = \begin{cases} 0 & \text{if } t \neq k \\ 1 & \text{if } t = k \end{cases}$  for  $k = 12, 24$  is the visit month
- $y_{i,j,t}$  is the MDS-UPDRS score at visit month  $t$
- $\delta_1$  is the slope coefficient for time  $t$
- $\delta_2$  is between group difference at 12 months
- $\delta_3$  is the between group difference at 24 months
- $U_{i,j} \sim N(0, \sigma_u^2)$  is the random effect for participant  $j$  in cluster  $i$ , independent of  $Z_i$
- $\varepsilon_{i,j,t} \sim N(0, \sigma_\varepsilon^2)$  is the individual residual error at month  $t$ .

The terms  $x_1$ ,  $x_{i,j}$ ,  $\theta$ ,  $Z_i$ ,  $i$  and  $j$  are the same as defined for Equation 2, except the baseline score which is now included as an outcome instead of a fixed effect covariate.

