### 6.2 ADJUSTMENTS

The primary analysis of the primary and secondary outcomes will include fixed effects adjustments baseline outcome, gender, age at baseline and modified Hoehn and Yahr score. Recruiting site will be included as a random effect in order to account for any potential unknown variation associated with each site.

In addition to the adjustments specified in the protocol, we will also include duration of PD, as recent evidence suggests that the rate of change in MDS-UPDRS differs according to disease duration. If there is a suggestion from a visual inspection of any large difference in any of the other baseline characteristics/ demographics between allocated groups, sensitivity analysis will include additional adjustments for such a covariate.

For completeness and in line with EMA guidance, the results of models only including adjustment for baseline scores (where available) will also be presented.

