#### 7.4.2 Disease-Modifying Analysis

If there is evidence from the primary analysis that Simvastatin is not futile, consideration will be given to performing additional analysis of the primary outcome to investigate a potential disease-modifying effect. Descriptive statistics (e.g. means and 95% CI) and plots of MDS-UPDRS part III by visit month and allocated group will be presented. Participants will be included in the disease modifying analysis if: (i) they have fully complied with the treatment protocol (i.e. definition (i) from section 4.4.2) and (ii) they have provided valid MDS-UPDRS III scores at least two time points according to the imputation requirements outlined in section 4.10.1.

A mixed effects, repeated measures model will be fitted to the primary outcome measured at baseline, 12, 24 and 26 months, with participants included as a random effect. This repeated measures model will allow for missing data, whilst also allowing for analysis of the two-period design of the washout phase.

Adjustments will also be made for the stratification variables, modified Hoehn & Yahr score as a fixed effect and recruiting site as a random effect, as well as patient-related factors, which may have a strong influence on disease progression, i.e. disease duration, gender and age at baseline, to account for potential influence on the primary outcome.

The repeated measure model to investigate a disease modifying effect is defined as

$$y_{i,j,t} = \delta^{12*} x_{1,i,j} I_{t=12} + \delta^{24*} x_{1,i,j} I_{t=24} + \delta^{26*} x_{1,i,j} I_{t=26} + \delta_1 t + \theta x_{i,j} + Z_i + U_{i,j} + \varepsilon_{i,j,t}$$

Equation 5

where  $\delta^{k*}$  is the allocated group difference at the  $k$  visit month. The terms  $y_{i,j,t}$ ,  $x_1$ ,  $\delta_1$ ,  $x_{i,j}$ ,  $\theta$ ,  $Z_j$ ,  $U_{i,j}$ ,  $\varepsilon_{i,j,t}$ ,  $I_{t=k}$ ,  $i$  and  $j$  are the same as defined in Equation 4, but  $k = 12, 24, 26$ , which include the 26-month visit and excludes baseline.

The study is not powered to determine whether the treatment is disease modifying. Therefore, the results of this analysis should be treated with caution, and interpreted as exploratory only. However, interpretation will focus on  $\delta^{26*}$ , where an estimate below zero may be indicative of a effect that persists after discontinuation of treatment, suggesting the possibility that the effect of simvastatin is disease modifying rather than merely symptomatic.

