## 8.2 SECONDARY OUTCOMES ANALYSIS

Continuous secondary outcome measures will be analysed:

- (i) at 24 months using mixed effects, linear regression models;
- (ii) across baseline, 12 and 24 months using repeated measures linear models.

Since incidence of diabetes is a binary measure only observed at 24 months, this secondary outcome will be modelled using a mixed effects logistic regression model.

The models will be adjusted by the covariates described in section 6.2, with the exception of the repeated measures models, which will not include the baseline measure as a covariate (as baseline data are included in the outcome being modelled).

As not all participants will be able to complete the 10MWT, the ability to complete the test, as well as the time, are both valuable indicators of PD progression. Therefore, we will analyse time and successful completion of the 10MWT as two components of this outcome measure.

We will model completing the 10MWT as:

- binary data – whether participant successfully completed at least one 10MWT (yes or no);
- continuous data - mean time, of participants who are able to complete at least one 10MWT.

The number of capsules and percentage of expected capsules returned every month will be reported for both of the allocated groups.

The secondary outcomes will not be tested under a futility hypothesis framework: allocated group differences will be assessed at the two-sided 5% level of significance and reported with two-sided 95% confidence intervals. As the trial is not powered to detect clinically meaningful differences on the secondary outcome measures, and no adjustments for multiplicity will be made, the results of the analyses of secondary outcomes will be interpreted and reported as exploratory only.

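### Equations 4 and 5 allow only a participant random intercept; if progression rates vary, the 24- and 26-month standard errors will tend to be too small, by about 2–3% at the SAP's planning SDs

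*SAP*

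**What the plan says.** SAP Section 7.4.1 fits the MDS-UPDRS part III score at three visits in a model that "will be fitted to the primary outcome measure at baseline, 12, and 24 months, where participants are included as a random effect". In Equation 4 the participant term U has one variance and the residual has one variance common to all visits. The time coefficient "is the slope coefficient for time" and is shared by everyone. Section 7.4.2 applies the same terms to the outcome "measured at baseline, 12, 24 and 26 months, with participants included as a random effect" (Equation 5). Neither section states a random slope, an unstructured or serial covariance, or robust standard errors.

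Section 6.2 adds disease duration as a covariate because "recent evidence suggests that the rate of change in MDS-UPDRS differs according to disease duration". Section 7.4.2 also treats duration, gender and age as possible strong influences on progression. In both equations these covariates enter without a time interaction.

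Section 8.2 analyses secondary outcomes "across baseline, 12 and 24 months using repeated measures linear models" and gives no covariance structure.

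**The concern.** A random intercept plus independent, equal-variance residuals is compound symmetry. Scores 26 months apart are assumed to correlate as strongly as scores 2 months apart, and the spread between participants is assumed not to grow. Given the covariates and group, everyone is taken to progress at one rate.

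If rates differ between participants, variance rises with time and correlation falls with the gap between visits. The fitted structure then averages smaller early variances with larger late ones and tends to understate uncertainty at the late visits. Those are the visits that matter here: the 24-month difference in Equation 4, reported with a two-sided 95% interval, and the 26-month difference in Equation 5, on which Section 7.4.2 says interpretation will focus.

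**Working it through.** **Plan's own figures (Section 4.2).** With SD 7.5, difference 3, one-sided 10% and 80% power: 2 × 7.5² × (1.2816 + 0.8416)² / 3² = 56.4, so 57 per group. Then 57/0.85² = 78.9, so 79; and 79/0.8 = 98.75, so 99 per group and 198 in total. These reproduce. The SAP gives no standard error or variance components for Equations 4 and 5, so there is no stated figure to check there.

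**Inputs.** From Section 4.2: SD of change 7.3 at 12 months and 7.5 at 24 months. Assumed: baseline SD 12, no intercept–slope correlation at first, complete data, 79 per group, covariates and site omitted. The SE ratio does not depend on the number per group.

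**Slope variance implied by the SAP.** With random intercept, random slope and residual, Var(change at t years) = σ_slope² t² + 2σ_e². Subtracting the 12-month from the 24-month variance gives 3σ_slope² = 7.5² − 7.3² = 2.96. So σ_slope² = 0.99 and the slope SD is 0.99 points/year.

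**Example, slope SD 2, 12-month change SD held at 7.3.** σ_e² = (53.29 − 4)/2 = 24.6. Intercept variance = 144 − 24.6 = 119.4. True variances at 0, 12 and 24 months are 144, 148 and 160. The true covariances are 119.4 (0–12), 119.4 (0–24) and 127.4 (12–24). The best-fitting compound-symmetry matrix takes the averages: variance 150.7 and covariance 122.0. Over four visits the true correlation is 0.78 for 0–26 months and 0.85 for 24–26 months; the model forces these to be equal.

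**Standard errors.** Let W be the fitted matrix, V the true one and X the printed mean structure (common intercept, linear time, group terms after baseline). The model-based variance is A⁻¹ with A = ΣX′W⁻¹X. The true variance is A⁻¹(ΣX′W⁻¹VW⁻¹X)A⁻¹. Coverage of a nominal 95% interval is 2Φ(1.96 × ratio) − 1.

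| Slope SD | 24-m change SD | Eq 4, 24 m: model / true SE | Ratio (coverage) | Eq 5, 26 m: model / true SE | Ratio (coverage) | Eq 4, 12 m ratio |
|---|---|---|---|---|---|---|
| 0.99 | 7.50 | 1.115 / 1.141 | 0.977 (94.5%) | 1.049 / 1.086 | 0.966 (94.2%) | 1.001 |
| 2 | 8.08 | 1.145 / 1.243 | 0.921 (92.9%) | 1.078 / 1.218 | 0.885 (91.7%) | 1.004 |
| 3 | 8.96 | 1.192 / 1.397 | 0.853 (90.5%) | 1.124 / 1.410 | 0.797 (88.2%) | 1.008 |

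**Intercept–slope correlation.** At slope SD 0.99 the ratios (Eq 4 at 24 m; Eq 5 at 26 m) are 1.00 and 0.99 with correlation −0.3, and 0.96 and 0.95 with +0.3. At slope SD 2 they are 0.96 and 0.93 with −0.3, and 0.89 and 0.86 with +0.3.

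**Simulation check.** 4000 trials, 57 per group, intercept SD 10, critical value 1.96. With slope SD 0, a nominal 5% test rejects 5.4% of the time (Eq 4, 24 m) and 5.6% (Eq 5, 26 m). With slope SD 0.99 it rejects 6.0% and 6.2%.

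**The case against.** The strongest reply is that the SAP's own numbers hardly show a problem. A random-intercept model implies equal SDs of change at 12 and 24 months, and 7.3 against 7.5 is nearly that. The larger shortfalls need slope SDs of 2–3 points/year and a 24-month SD of 8.1–9.0, none of which the SAP states. This stands, and it makes the size conditional. It does not settle the matter the other way, because 7.5 is a planning inflation and not an estimate.

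The stakes are also limited. Equation 2 uses one change score per participant, so the futility test is untouched. The 26-month analysis is conditional, unpowered, exploratory and read mainly on the sign of the estimate. This stands too. The bootstrap in Section 6.1 is only a partial safeguard, because its trigger is not tied to the covariance.

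A reader might infer more than the SAP supports:
- *That the late standard errors are too small as a matter of fact.* This depends on a slope variance and a correlation that the SAP does not give; a correlation of −0.3 nearly removes the effect at the planning SDs.
- *That the 12-month interval is materially too wide.* With zero correlation and the printed linear time term it is within 1%. An excess of 3–6% appears only if visit is fitted with separate means.
- *That Section 6.2 proves residual slope variation.* It says rates differ by disease duration, a measured covariate, for which a duration-by-time term would be the direct response.
- *That the statement "This repeated measures model will allow for missing data" fails.* Likelihood-based handling of missing visits does lean on the covariance, but the calculation used complete data and shows no bias.
- *That the Section 8.2 models share the structure.* The SAP does not say.

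**Conclusion.** The point holds as a conditional weakness in two non-primary models. Equations 4 and 5 impose compound symmetry, and if progression rates vary the standard errors of the 24- and 26-month differences will tend to be too small. With zero intercept–slope correlation, assumed baseline SD 12 and 12-month change SD 7.3, the shortfall is:

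- about 2% (24 m, Eq 4) and 3% (26 m, Eq 5) at the SAP's planning SDs;
- about 8% and 12% at an assumed slope SD of 2 points/year;
- about 15% and 20% at an assumed slope SD of 3 points/year.

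The reading of the equations is certain; the size is not. It is a worthwhile improvement to the specification and does not threaten the trial's main conclusion.

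**What to change.** In Equations 4 and 5, replace the participant random intercept and independent residuals by an unstructured within-participant covariance across visits (3×3, or 4×4 with 26 months). Keep the site random intercept, fit by REML and use small-sample degrees of freedom. Name the fallback if the model does not converge: random intercept and slope, or random intercept with robust standard errors. Non-convergence is more likely for the 4×4 matrix, because Equation 5 is limited to participants compliant under definition (i). State the covariance for the Section 8.2 repeated measures models as well.

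The cost is a change of wording and a model option. Variance parameters rise from 2 to 6 with three visits (4 extra) and from 2 to 10 with four (8 extra), which is a small loss if compound symmetry is in fact adequate.

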### **4.3 STATISTICAL SIGNIFICANCE LEVELS**

As this is a futility study, a one-sided test of the primary outcome is appropriate, which has been set at the 10% significance level. All other outcome variables will be assessed on a two-sided test at the 5% significance level with corresponding two-sided 95% confidence intervals.

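### Equations 4 and 5 use a single linear time slope where Section 7.4.1 describes visit terms, so a non-linear course shared by both arms can appear as a group difference

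*SAP*

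**What the plan says.** The text of SAP Section 7.4.1 reads: "The model will include visit (baseline, 12 months and 24 months) and the interaction between visit and allocated group". Equation 4, directly below it, has no visit main effects. Its time part is one term, δ₁t, and δ₁ "is the slope coefficient for time" t, so t is a number of months and not a factor. The remaining time-related terms are the allocation indicator x₁ multiplied by I(t=12) and by I(t=24). Their coefficients are defined so that δ₂ "is between group difference at 12 months" and δ₃ "is the between group difference at 24 months".

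Section 7.4.2 states: "A mixed effects, repeated measures model will be fitted to the primary outcome measured at baseline, 12, 24 and 26 months". Equation 5 takes δ₁ over from Equation 4 and gives simvastatin a free term at k = 12, 24 and 26, "which include the 26-month visit and excludes baseline". Interpretation rests on δ²⁶*, "where an estimate below zero may be indicative of a effect that persists after discontinuation of treatment".

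A linear course is assumed in one other place, Section 4.2, where it serves only to extrapolate 2.2 points at 12 months to 4.4 points at 24 months for the sample size.

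**The concern.** An analyst who follows the text of Section 7.4.1 and one who follows Equation 4 would fit different models. The equation's version ties the placebo arm to a line through the shared baseline and lets each simvastatin mean after baseline go where the data put it. If both arms bend in the same way, for example through an early placebo response or a change when trial capsules stop at 24 months, the placebo line cannot follow. The misfit is absorbed by the coefficients that are meant to measure the drug.

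Equation 4 is the planned analysis of the primary outcome that can use participants who have no 24-month score. Equation 5 is the model in which the SAP looks for a persisting effect on that outcome. A spurious 12-month or 26-month difference would therefore be reported as evidence about simvastatin.

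**Working it through.** **1. Implied means** (a = common baseline mean)

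| Visit | Placebo | Simvastatin |
|---|---|---|
| 0 | a | a |
| 12 | a + 12δ₁ | a + 12δ₁ + δ₂ |
| 24 | a + 24δ₁ | a + 24δ₁ + δ₃ |

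With a common baseline there are 5 distinct means but only 4 parameters, so one constraint (placebo linearity) is imposed. In Equation 5 there are 7 means and 5 parameters, so there are two constraints.

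**2. Inputs**

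- From Section 4.2: placebo change 2.2 at 12 months and 4.4 at 24 months; SD of the 24-month change 7.5.
- Group sizes, also from Section 4.2: 2 × (1.2816 + 0.8416)² × 7.5² / 3² = 56.3, giving 57 per group (power 80.1% by the noncentral t). Then 57/0.85² = 78.9, giving 79, and 79/0.8 = 98.75, giving 99. The plan's figures reproduce. Both 57 and 79 are used below.
- Residual variance: under a random intercept, the variance of a change is 2σₑ², so σₑ² = 7.5²/2 = 28.1.
- Assumptions not in the SAP: between-participant SD σᵤ, ranged 5 to 14, and the size of any departure from the line. Data are taken as complete. Site and covariates are left out.
- Yardstick: two-sided 5%. Section 4.3 sets that level for outcome variables other than the primary; the SAP does not state a level for this re-analysis of the primary outcome.

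**3. Formula.** Both arms are given the same mean vector μ (inert drug). With V = σₑ²I + σᵤ²J, the expected estimates are (ΣX′V⁻¹X)⁻¹ ΣX′V⁻¹μ, and the SEs come from the same inverse. With b the bias, the rejection rate is Φ(-1.96 - b/SE) + Φ(-1.96 + b/SE).

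**4. Equation 4**, both arms at 0, 2.2 + c, 4.4. Ranges run from σᵤ = 5 to σᵤ = 14.

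| c | Expected δ₂ | Expected δ₃ | Rejection for δ₂, 57 per arm | Rejection for δ₂, 79 per arm |
|---|---|---|---|---|
| 0 | 0 | 0 | 5% | 5% |
| -1 | -0.86 to -0.97 | +0.18 to +0.04 | 15% | 18% |
| -2 | -1.72 to -1.94 | +0.37 to +0.08 | 43% | 56% |
| -2.2 | -1.90 to -2.13 | +0.41 to +0.09 | about 50% | 64% |

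Example: c = -2, σᵤ = 8, 57 per arm. Here b = -1.84 and SE = 1.03, so b/SE = -1.79 and Φ(-1.96 + 1.79) ≈ 0.43. The test of δ₃ rejects in 5% to 7% throughout.

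**5. Equation 5**, both arms linear to 24 months and then 2 points below the line at 26 months.

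- δ²⁶* = -0.78 to -0.88, rejecting in about 9% to 12% at 57 per arm and 11% to 15% at 79.
- δ²⁴* = +1.03 to +1.13, rejecting in about 15% to 16% at 57 per arm and 19% to 20% at 79.
- A 2-point dip at 12 months alone gives δ¹²* = -1.89 to -2.13 but moves δ²⁶* by only -0.02 to -0.33.
- A shared upward step reverses the signs. For both arms at 0, 2.2, 4.4, 7.4, δ²⁶* is about +1.0 to +1.2 and δ²⁴* about -1.4 to -1.5.

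**6. Same scenarios with visit indicators.** Every group-difference coefficient is 0 and rejection is 5%.

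**The case against.** The strongest reply is that little turns on these models. The futility decision uses Equation 2, a 24-month change model with no time term. In Equation 4 the coefficient at the primary time point, δ₃, is nearly unbiased. Under the linear course assumed in Section 4.2 there is no bias at all, and the largest bend shown needs no progression for a year followed by all 4.4 points in the next. Section 7.4.2 is conditional on a non-futile result and labelled exploratory, and its planned means and plots by visit and arm would show a shared bend. All of this stands, and it limits the severity. It does not settle which model is to be fitted.

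Some stronger readings are tempting but not supported:

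- *Both sections contradict their equations.* The explicit mismatch is in Section 7.4.1. Section 7.4.2 does not list visit as a model term; Equation 5 inherits the slope.
- *A worsening step in washout would create a false disease-modifying signal.* It biases δ²⁶* upward, against the drug. Only a shared drop below the line pushes it in the direction the SAP reads as favourable.
- *This is the only look at disease modification.* Table 3 also assigns the 10 metre walk test and levodopa-equivalent dose to that question.
- *The random intercept is itself an error.* It is a conventional choice, and nothing in the SAP allows its effect to be sized.
- *δ₃ ought to be tested against -3.* The Section 4.3 sentence, "All other outcome variables will be assessed on a two-sided test at the 5% significance level", concerns other outcome variables. The SAP is silent on how δ₃ relates to the margin, so such a test would be an added analysis and not the correction of an error.

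**Conclusion.** The point holds as an inconsistency that should be fixed. Section 7.4.1 describes visit terms, Equation 4 fits a line, and Equation 5 extends that line through washout. The mechanism is exact: any departure from linearity shared by both arms enters the group-difference coefficients. Its size is conditional on the assumed curvature and σᵤ. In Equation 4 the harm falls on the 12-month difference; in Equation 5 it reaches the 24-month and 26-month differences when the arms leave the line after treatment stops. The documents do not show that the course will be non-linear, so they do not support saying that these estimates will be biased, only that the equations leave them unprotected. The primary futility conclusion and the sample size are not touched.

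**What to change.** In Equation 4, replace δ₁t by separate coefficients for I(t=12) and I(t=24). In Equation 5, do the same and add I(t=26). Keep the common baseline mean, and amend the definition of δ₁ to match. For Equation 4 this is the model the Section 7.4.1 text already describes.

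The cost is one extra parameter in Equation 4 and two in Equation 5, plus the SAP wording. The SE of the 12-month difference in Equation 4 rises from about 0.9 to 1.1 at 79 per arm (at 57 per arm and σᵤ = 8, from 1.03 to 1.29). The 24-month SE in Equation 4 is essentially unchanged (1.29 in both versions at 57 per arm and σᵤ = 8). In Equation 5 the 24- and 26-month SEs also rise somewhat (same setting: 1.17 and 1.21, each to 1.29). Nothing changes in trial conduct or data collection.
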